## Abstract

**Introduction:**

Physical literacy (PL) is a multidimensional construct encompassing motivation, confidence, physical competence, knowledge, and understanding, which is essential for fostering lifelong physical activity. University students represent a critical stage for PL development, yet many experience a decline in physical activity and an increase in sedentary behavior after high school. Sports video games (SVGs), though traditionally sedentary, have shown potential to enhance motivation and cognitive engagement with sports. These games are especially popular among university students, making them an accessible and engaging tool for promoting PL. Despite their popularity, the role of SVGs in supporting PL development remains underexplored, particularly in Asian contexts. Integrating technology into physical education, such as through SVGs and virtual simulations, may offer innovative ways to enhance engagement and support PL development. Although the intervention is sedentary, SVG gameplay often requires reflexes and eye–hand coordination which may influence aspects of physical competence such as reaction time and coordination. This study aims to evaluate whether a tennis-themed SVG intervention integrated into PE lessons can enhance students’ motivation, sport-specific knowledge, physical competence, social engagement, and physical activity engagement, thereby promoting holistic PL development.

**Methods:**

A cluster randomized controlled trial will be conducted with 176 first-year students enrolled in compulsory tennis physical education courses at The Chinese University of Hong Kong. Eight entire classes (four male and four female) will be randomly assigned to either an intervention or control group. The intervention group will play a tennis SVG, *TopSpin 2K25,* twice weekly for six weeks alongside regular PE lessons. Assessments at baseline, post-intervention, and three-week follow-up will include self-reported gaming behavior, physical activity level, PL domains, and objective tests of reaction time, eye-hand coordination, and tennis knowledge.

**Discussion:**

This protocol examines the integration of SVG into physical education to promote PL across physical, cognitive, affective, and social domains. Limitations include potential contamination bias, variability in prior gaming experience, short intervention duration, and reliance on self-reported measures, which may introduce bias. Theoretically, the study advances PL frameworks by embedding technology-enhanced learning within structured PE contexts. Practically, SVG-based activities offer an inclusive, engaging approach to support diverse learners. Future research should explore long-term effects and develop validated tools for comprehensive assessment.

**Trial registration:** The protocol has been registered on the Open Science Framework on 25 July 2025: https://doi.org/10.17605/OSF.IO/JDYGV.

## Introduction

Physical literacy (PL) is increasingly recognized as a foundational concept in physical education, encompassing the motivation, confidence, physical competence, knowledge, and understanding necessary for individuals to value and engage in physical activity throughout life [1]. For university students, who are transitioning into adulthood and independence, developing PL is particularly critical. This stage is often considered the final opportunity within formal education to instill essential PL attributes and foster a lifelong positive attitude toward physical activity [2]. However, after graduating from high school, many adolescents show a decline in physical activity participation [3], alongside a rise in sedentary leisure behaviors [4]. These trends present significant challenges to the development of sustainable physical activity habits and comprehensive PL. While PL is widely accepted as a guiding framework, ongoing theoretical debates persist regarding its measurement and operationalization. For example, Boldovskaia et al. [5] emphasize that despite PL’s conceptual acceptance, there is considerable debate over appropriate methods for collecting empirical data, with most existing instruments focusing narrowly on certain dimensions.

Traditional physical education (PE) programs have primarily focused on developing motor skills and fitness, often overlooking opportunities to integrate technology-driven approaches that can enhance engagement and learning. Recent advancements in educational technology have opened new pathways for promoting PL through interactive and immersive experiences. AI-assisted interactive systems have demonstrated increased engagement and comprehension in technology-mediated environments, supporting the educational potential of game-based interventions [6]. These systems leverage adaptive feedback and personalized learning to create dynamic environments that foster motivation and skill acquisition. In the context of PE, sports video gaming (SVG) represents a promising application of these principles, offering students an engaging platform to practice decision-making, strategy, and collaboration while reinforcing physical skills.

Beyond PL, previous research indicates that structured physical activity interventions can yield significant psychological and physiological benefits, including mood regulation, emotional resilience, and neurochemical modulation [7]. These findings underscore the broader role of physical engagement through innovative modalities such as SVGs to promote PL, enhance motivation, and support overall health among university students.

At the same time, video gaming has become the most popular form of entertainment among adolescents and young adults worldwide. Traditional video games are typically played in a stationary posture using simple hand or finger movements, and are therefore considered a form of sedentary behavior [8]. Among these, SVGs are especially popular among adolescents. In 2024, five SVGs ranked among the top ten best-selling titles in the United States, including *EA Sports College Football 25*, *NBA 2K25* and *Madden NFL 25* [9]. SVGs simulate traditional sports using handheld controllers to manipulate on-screen avatars in a seated position [10]. Despite their sedentary nature, research has shown that SVGs can increase motivation and interest in participating in real-life sports among youth and adolescents [11–14]. According to Adachi and Willoughby [11], playing SVGs can foster a sense of competence and mastery, which boosts self-confidence and encourages involvement in physical sports. SVGs also simulate sports environments and strategies, increasing cognitive familiarity and reducing barriers to real-world participation. Additionally, studies suggest that SVGs can be effective tools for teaching sports-related knowledge, such as rules, strategies, and tactics especially for beginners [13,15,16].

While existing research has largely focused on the affective and cognitive benefits of SVGs, there remains a notable gap in studies exploring their influence on physical competence and the social domains of PL [17]. Crucially, the PL construct consists of four interrelated elements (motivation/confidence, physical competence, knowledge/understanding, engagement in physical activities for life) and respective domains (affective, physical, cognitive, behavioral) [18]. Improvements in one domain can positively influence others; for example, greater motivation may increase activity participation, enhancing physical competence and confidence, while deeper sport-specific knowledge can foster meaningful social interactions. SVGs, by stimulating motivation and cognitive engagement, may serve as a catalyst for holistic PL development. Moreover, gameplay often involves perceptual-motor demands such as reflexes and coordination and incorporates cooperative or competitive social interactions. These considerations underscore the need for interventions addressing all PL domains rather than focusing narrowly on motivation or knowledge.

In this study, simple reaction time and eye–hand coordination were selected as outcome measures because they represent targeted components within the physical domain of PL and align with the perceptual–motor demands of both video gaming and real-life tennis. While these measures do not capture comprehensive motor competence, they provide insight into specific physical attributes that may be influenced by the intervention.

A tennis-themed SVG intervention was selected for this study based on the limited exposure to tennis among university students in Hong Kong. Tennis is not commonly taught in primary or secondary education, resulting in most students entering university with minimal prior experience in the sport. Teaching tennis in PE classes for beginners presents several challenges. Due to time constraints and varying skill levels, it is difficult to cover all fundamental techniques and tactical concepts, and students may struggle to apply what they learn in real game situations. The selected SVG (TopSpin 2K25) is a well-developed and immersive tennis simulation that addresses these limitations by providing repeated exposure to tennis rules, scoring systems, basic techniques, and gameplay strategies in a visually engaging and easy-to-understand format. This allows students to build sport-specific knowledge and decision-making skills at their own pace, complementing the learning objectives of the PE curriculum.

The intervention leverages specific game mechanics to target PL domains and foster motivation for real-life tennis participation rather than increased video gaming. Fast-paced rally sequences and timing-based challenges aim to improve perceptual-motor skills such as reaction time and eye-hand coordination (physical domain). In-game tutorials and rule-based decision-making tasks support sport-specific knowledge (cognitive domain). Immersive graphics, realistic physics, and authentic match scenarios are designed to enhance enjoyment and create a sense of competence, which may translate into motivation to engage in actual tennis (affective domain). Multiplayer modes encourage peer interaction and collaboration (behavioral domain). Together, these mechanics are intended to promote multidimensional PL development and bridge virtual engagement with real-world physical activity.

The intervention is designed to be flexible, allowing it to enhance rather than replace traditional PE instruction. Since the SVG does not require formal teaching and students engage with the game independently, it can be integrated as a supplementary activity outside of scheduled PE class time. This approach enables students to reinforce and extend their learning of tennis-related concepts without interfering with the core instructional time allocated for physical skill development. The SVG provides additional opportunities for cognitive engagement and sport-specific knowledge acquisition, supporting the broader goals of PL.

Despite growing interest in the educational and motivational potential of SVGs, intervention studies utilizing these tools to promote PL remain limited, particularly in Asian contexts [17]. Most existing research has been conducted in Western settings, leaving a gap in understanding how culturally relevant applications of SVGs may influence PL and physical activity behaviors in Asian populations.

Therefore, the aim of this study is to investigate the effectiveness of a tennis-themed SVG intervention, implemented alongside regular PE lessons, in promoting holistic PL among university students in Hong Kong. Specifically, the study will evaluate whether SVG participation can enhance motivation, sport-specific knowledge, physical competence, social engagement, and physical activity engagement. Using a cluster randomized controlled trial design, this research seeks to identify innovative, technology-enhanced strategies to improve PE outcomes and foster lifelong physical activity.

Following the intervention and subsequent follow-up, we hypothesize that:

*Physical Competence***:** Participants in the intervention group will demonstrate greater improvement in perceptual-motor skills, specifically simple reaction time and eye-hand coordination, compared to those in the control group. These measures represent targeted components within the physical domain of PL and align with the perceptual-motor demands of both sports video gameplay and real-life tennis, rather than comprehensive motor competence.*Motivation for real-life sports***:** Participants in the intervention group will report a greater increase in motivation to engage in real-life sports compared to those in the control group.*Cognitive knowledge of tennis:* Participants in the intervention group will achieve a greater improvement in cognitive knowledge related to tennis than participants in the control group.*Social engagement in physical activities*: Participants in the intervention group will exhibit greater enhancement in in-person social interaction relative to the control group.*Physical activity engagement:* Participants in the intervention group will show a higher increase in physical activity engagement levels than their counterparts in the control group.

## Materials and methods

### Study design

A cluster randomized controlled trial will be conducted to examine the effectiveness of participation in the tennis SVG ‘*TopSpin 2K25’* on PL among university students at the Chinese University of Hong Kong (CUHK), beyond their regular tennis PE lessons. In this context, the PE courses refer specifically to the public PE practice courses that are compulsory for non-sports majors, guided by PE teachers, which are credit-bearing. Our study employs cluster randomization at the class level, rather than individual randomization, which is commonly used in educational setting. This approach allows entire classes to be randomly assigned to either the intervention or control group, maintaining the integrity of existing class structures and minimizing disruption to timetables and teaching logistics.

A total of 176 first-year university students enrolled in tennis PE courses will be recruited. These students will be drawn from eight entire classes – four male and four female, with each class comprising 22 students. Although students self-select their PE classes during course registration, random assignment will be conducted at the class level after enrollment is finalized. The classes will be randomly assigned to either the intervention group (two male and two female classes; 88 students) or the control group (two male and two female classes; 88 students).

The intervention group will engage in two 20-min sports video gaming sessions weekly in addition to their regular PE lessons. The intervention will last for six weeks, followed by a three-week follow-up period. Data will be collected at three time points: baseline, post-intervention, and follow-up. The intervention duration of two 20-minute sessions per week was selected based on feasibility within the university schedule and supported by prior research. Röglin et al. [19] conducted a randomized controlled trial in which 15–20-minute exergaming sessions, delivered twice weekly over three months, significantly improved students’ physical self-concept, including strength, coordination, and speed. These findings suggest that even short-duration, structured gaming interventions can elicit measurable changes in physical competence and support physical literacy development.

The study design, implementation and reporting of the results will adhere to the Standard Protocol Items: Recommendations for Interventional Trials (SPIRIT) guidelines [20]. This study protocol was prospectively registered on the Open Science Framework (OSF) on 25 July, 2025. The full protocol is accessible at: https://doi.org/10.17605/OSF.IO/JDYGV.

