### Eligibility criteria and recruitment

Eligible participants must be first-year students enrolled in the required tennis PE course, aged 18 or above, and free from any disabilities, injuries, or illnesses that would impair their ability to perform daily tasks. Students with a regular habit of playing *TopSpin 2K25* will be excluded.

This study is scheduled to begin in the first week of the second semester of the 2025–2026 academic year in CUHK. A briefing session and participant recruitment will be conducted during the week of 5 January 2026, integrated into the schedule tennis PE lessons. Recruitment will conclude on 16 January 2026, coinciding with the end of the university’s add-drop period, at which point the class lists will be finalized. Recruitment will take place during the first lesson in the PE tennis courses, where teachers will explain the study and distribute consent forms. An introductory meeting will be held with the teachers to outline the intervention procedures and assessment methods. Additionally, a training workshop will be provided for research assistants and student helpers, covering gameplay instructions and guidelines for facilitating the gaming sessions.

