### Data collection

This study will employ both self-reported and objective measures to comprehensively assess participants’ PL, engagement in physical activities, and sports video gaming habits.

Self-reported data will be collected through a structured set of online questionnaires (see Appendix 1), which include items on video gaming behavior, physical activity levels, physical literacy, and demographic information. These questionnaires will be administered by trained research assistants using Qualtrics, a secure and institution-approved online survey platform. Access to the survey will be provided via a secure link or QR code, distributed to students by their teachers.

Objective measures will include assessments of simple reaction time and eye-hand coordination, conducted using the Ruler Drop Test (RDT) and the Alternate Hand Wall Toss Test (AHWT), respectively. Additionally, a knowledge-based quiz will be administered to evaluate participants’ cognitive understanding of tennis (see Appendix 2).

All assessments will be conducted during scheduled PE tennis lessons at the CUHK. Data collection will occur at three time points: baseline, post-intervention, and a three-week follow-up. Baseline data collection is scheduled for the first week of the second semester (early January 2026), during the same lesson in which participants are recruited. This will be followed by a six-week sports video gaming (SVG) intervention. Post-intervention assessments will be conducted in Week 8 (early March 2026), and a three-week follow-up assessment will take place in Week 11 (late March 2026).

The participant timeline is illustrated in Fig 1. To ensure consistency across all groups, identical procedures and instruments will be used. All assessments will be administered by the principal researcher in collaboration with trained research assistants. A summary of the measurement tools and outcome variables is provided in Table 1.

**Table 1 pone.0343594.t001:** Summary of measurements in this study.

Instrument/Method used	Outcome assessed	Type	Physical literacy domain	Reference
Custom questionnaire on video gaming	Video gaming habits and demographics	Self-reported	Not applicable	Developed by researcher
International Physical Activity Questionnaire – Short Form (IPAQ-SF)	Physical activity level	Self-reported	Physical	[22]
Perceived Physical Literacy Instrument (PPLI)	Perceived physical literacy	Self-reported	Affective, social, cognitive	[23]

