**Fig 1 pone.0343594.g001:**
[figure not shown]
Participant timeline schematic diagram. Week 1 included briefing, enrollment, and baseline assessment. Weeks 2-7 comprised the 6-week SVG intervention. Post-intervention assessment was conducted in Week 8, followed by a 3-week follow-up assessment in Week 11.

1. **Demographic information**

Participants will provide demographic details including age, gender, ethnicity, academic department and faculty, sports regularly participated in, and years of involvement in those sports. The details will be collected in the beginning of the online questionnaire.

2. **Self-reported measures**

To capture participants’ behaviors and perceptions across relevant domains, a series of self-reported instruments will be administered via an online questionnaire.

i) *Video gaming habit*

Participants will respond to questions regarding their video gaming behaviors, including frequency, duration, devices used, and types of games played. Sample items include:

“How much time per week you play video games?”“How many days per week do you play video games?”“How long have you been playing video games?”

Participants who indicate regular gaming activity will be asked additional questions specific to sports video gaming (SVG), such as:

“Which types of sports video games you play?”“How much time per week you play sports video games?”“How many days per week do you play sports video games?”

ii) *Physical activity level*

Participants’ physical activity levels will be assessed using the International Physical Activity Questionnaire – Short Form (IPAQ-SF)**.** This instrument evaluates the frequency and duration of physical activities across different intensities: vigorous, moderate, and walking, as well as time spent sitting, over the past seven days. It provides an estimate of total physical activity expressed in MET-minutes per week. A sample item includes:

“During the last 7 days, on how many days did you do vigorous physical activities like heavy lifting, digging, aerobics, or fast bicycling?”

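### The randomisation rule, the date class lists close, the week numbering and the March assessment date do not reconcile, so it is unclear whether allocation precedes the end of add-drop

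*Protocol article*

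**What the plan says.** Four parts of the protocol article bear on the order of events.

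- **Study design.** Students choose their own PE class at registration. Against that background the protocol states that "random assignment will be conducted at the class level after enrollment is finalized".
- **Eligibility criteria and recruitment.** "A briefing session and participant recruitment will be conducted during the week of 5 January 2026". The closing date follows: "Recruitment will conclude on 16 January 2026"; this is the last day of add-drop, when the lists become final. Students are to be recruited in the first lesson.
- **Data collection.** "Baseline data collection is scheduled for the first week of the second semester (early January 2026"), in the same lesson as recruitment. Later: "Post-intervention assessments will be conducted in Week 8 (early March 2026").
- **Fig 1 legend.** Week 1 holds the briefing, enrolment and baseline. Then: "Weeks 2-7 comprised the 6-week SVG intervention".

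The Randomization section describes drawing lots but gives no date for the draw. No section gives a calendar date for Week 2 or for the first gaming session.

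**The concern.** Students pick their own classes, so allocating classes only once the lists are closed is the protocol's own safeguard against students sorting themselves into arms. The safeguard works only if nobody knows the allocation while class changes and consent are still open.

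Read in sequence from the week of 5 January, the week numbering starts gaming sessions before the lists close. Those sessions cannot be run without an allocation. Following the numbering would therefore mean drawing lots early. Students could then move into or out of a gaming class knowing what it is, and anyone recruited late would consent knowing their arm. With eight classes, four per arm, such movement changes the make-up of the arms directly, and covariate adjustment cannot reliably undo it.

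Baseline is a related matter. It is scheduled in the first-week lesson, while recruitment stays open to 16 January. No baseline slot is stated for a student who joins a class after its first lesson. The hypotheses concern improvement over time, and the Data analysis section adjusts all models for baseline physical activity.

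**Working it through.** **Inputs from the protocol**
- Week 1 (briefing, enrolment, baseline) is the week of 5 January 2026, a Monday (Eligibility criteria and recruitment; Data collection; Fig 1 legend).
- Class lists are final on 16 January 2026, a Friday (Eligibility criteria and recruitment).
- Allocation comes after that (Study design).
- The intervention runs in Weeks 2 to 7 (Fig 1 legend).
- Week 8 is in early March 2026 (Data collection).

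**Step 1: try to reproduce the stated Week 8 date.** With consecutive weeks, the Monday of Week w is 5 January + 7 × (w − 1) days.
- Week 2: 5 January + 7 days = 12 January, so 12 to 16 January.
- Week 7: 5 January + 42 days = 16 February, so 16 to 20 February.
- Week 8: 5 January + 49 days = 23 February, so 23 to 27 February.

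The early-March date is not reproduced. The first Monday-to-Friday week of March is 2 to 6 March, one week later.

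**Step 2: compare Week 2 with the closing of the lists.** On the same count, the lists close on the last weekday of Week 2. An allocation made after 16 January cannot exist when Week 2 sessions would open on 12 January.

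**Step 3: see where one extra week could go.** The early-March date needs one more week than the numbering provides. There are three ways to supply it:

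| Reading | Week 2 | Week 7 | Week 8 | Consequence |
|---|---|---|---|---|
| Unnumbered week before Week 2 | 19–23 January | 23–27 February | 2–6 March | Intervention starts after lists close; March date met |
| Unnumbered week after Week 2 and before Week 8 | 12–16 January | depends on where it falls | 2–6 March | March date met; Week 2 still inside add-drop |
| Week 1 moved to 12–16 January | 19–23 January | 23–27 February | 2–6 March | March date met; conflicts with recruitment and baseline in the week of 5 January |

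The protocol states none of the three. The first two both assume a week that is not mentioned.

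**Step 4: check that the safe order is feasible.** The Mondays after 16 January and before March are 19 and 26 January and 2, 9, 16 and 23 February. That gives six full Monday-to-Friday weeks, 19 January to 27 February, which is the planned length of the intervention.

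**The case against.** The strongest reply is that the protocol never dates Week 2. The 12 January start is an inference from counting weeks, and the same count misses the protocol's own date for Week 8. Counting back from 2 to 6 March puts Week 2 at 19 to 23 January, immediately after the lists close, and everything then fits. Since recruitment runs to 16 January, the Week 1 label in the figure legend may describe a phase longer than one calendar week. The rule on when to randomise is stated plainly, and nothing says it will be broken. Catch-up baseline testing is a detail that an article may leave to the full protocol, and a student recruited at a second lesson could be assessed then, before the draw.

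Much of this stands. It shows that a sound schedule exists and that early disclosure is not a planned step. It does not show that the sound schedule is the one printed. That schedule needs an unnumbered week before Week 2, and a break placed later would restore the March date while leaving Week 2 inside add-drop. Staff working from Fig 1 have no text telling them which applies.

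A reader might infer three stronger points, none of which the document supports:
- That the six weeks cannot be delivered if allocation waits for 16 January. Six full weeks remain before March.
- That Week 2, or 2 of 12 sessions (17%), is lost. This requires Week 2 to be 12 to 16 January, which is not stated, and the protocol also provides make-up sessions.
- That the Week 11 date is a further clear error. The consecutive count gives 16 to 20 March, against a stated late March, and that difference is too loose to rely on.

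**Conclusion.** The point holds as an internal inconsistency at the step that protects the allocation. The randomisation rule, the list-closing date, the week numbering and the early-March assessment cannot all be met with consecutive weeks counted from 5 January; the discrepancy is about one week.

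The consequence is conditional. If the week numbering is followed, allocation is disclosed during add-drop and selection into arms becomes possible. If the March date is followed and the extra week falls before Week 2, the order is sound and no exposure is lost. The size of any resulting bias cannot be computed from the document, because it depends on how many students would change class or join late.

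The conclusion assumes that Week 1 is the week of 5 January, as the recruitment and baseline statements indicate, and that weeks are numbered consecutively unless the text says otherwise. It should be settled before the draw, because disclosure in the wrong order cannot be reversed.

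**What to change.** 1. Make the Study design rule binding. State that the lots are drawn, and the result disclosed to teachers and students, only after class lists close on 16 January 2026, and that the first gaming session comes after that. Give the dates of the draw and of the first session.
2. State that students who join a class after its first lesson complete baseline before the draw.
3. State that students are analysed according to the class they belonged to at the draw.
4. Reconcile the week numbers and calendar dates in Eligibility criteria and recruitment, Data collection and Fig 1. If there is an unnumbered week, say where it falls.

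The cost is timetable wording and one catch-up baseline at an existing lesson. The sample size and the analysis model are unaffected.
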